**Figure 3 F3:**
[figure not shown]
**CONSORT flow diagram**.

To assess compliance with the study protocol, the amounts of PN and EN actually given in the two study groups during the intervention window of 8 days will be reported as absolute numbers and percentages of target calories.

Discrete variables will be summarized by frequencies and percentages. Continuous variables will be summarized by use of either mean or standard deviations (SD) or median and interquartile range as appropriate.

Baseline and outcome variables will be compared using Student's t-test, (exact) Chi-square test and Mann-Whitney-U test, as appropriate.

All outcomes will be analyzed in an uncorrected manner as well as jointly corrected for risk factors (type and severity of illness, age, BMI and NRS categories). Type of illness will comprise the diagnostic categories, as stratified and grouped per organ system, as well as the presence or absence of a history of cancer. As severity of illness score for this correction, APACHE II will be used. BMI will be categorized as <20, 20-<25, 25-<30, 30-<40 and ≥40 kg/m2. Applicable NRS categories for this study are 3, 4, 5, 6 and 7. In case certain categories would appear underrepresented, such patients will be assigned to the next category in rank or previous category if it is the last category that is underrepresented.

A priori defined subgroup analyses will be performed for BMI and NRS subcategories. These subgroup analyses are based on the rationale that BMI has been reported to be associated with different risk of outcome in different types of ICU patients which may be due to different handling of nutritional substrates [36-38]. This risk appeared different for patients with overweight or obesity (BMI 25 to <40) versus all other BMI categories (undernourished and normal BMI [BMI <20 and BMI 20-<25] or morbid obesity [BMI ≥ 40]). Therefore BMI will be dichotomized as such to optimize the power of this subgroup analysis. Also patients at higher risk of malnutrition may respond differently to the feeding strategies. Therefore, in this subgroup analysis, NRS will be dichotomized separating the highest risk patients [NRS ≥ 5] from the moderate risk patients [NRS 3 and 4]. Another a priori defined subgroup analysis will be performed for patients admitted to ICU after emergency or elective cardiac surgery as compared with all other patients. The shorter time in ICU of this subgroup may result in the early PN group receiving predominantly extra glucose 20% infusion, without lipids and amino-acids, as compared with the glucose 5% in the late PN group, which may evoke a different response than the full week combined parenteral nutrition. As sepsis is known to aggravate the metabolic disturbances evoked by early PN, a priori subgroup analysis is planned for patients with and without sepsis upon admission. These a priori defined subgroup analyses will be performed for the primary and safety endpoints without correction for other variables. To test for interaction between the identified subgroups and the studied intervention, a multivariable analysis (logistic regression or proportional hazard analysis as appropriate) will be performed for each subgroup variable separately and with the subgroup variable, the intervention and their interaction in the model. The interaction will be tested at a significance level of 0.1.

The first clinical report will analyze the impact of the nutritional strategies on safety (among which mortality), primary and secondary efficacy endpoints.

For all endpoints, differences will be considered statistically significant whenever the p-value reaches 0.05 or lower without correction for multiple testing.

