### Data collected at study entry

At baseline, data on demographic and clinical characteristics of the patients are obtained. Disease specific risk scores are calculated and co-morbidities and known use of important medications prior to admission are noted: these comprise, among others, Acute Physiology and Chronic Health Evaluation II score (APACHE II), presence of cancer, diabetes mellitus, kidney failure (Chronic Kidney Disease score), liver failure (Child classification), COPD (Gold classification), and heart failure (New York Heart Association Functional Classification ≥ 2). Sepsis upon admission is labeled as such using modified Bone criteria [30,31].

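### The common correction set omits sepsis on admission, a recorded baseline factor, so the corrected models give up a small amount of power; adding it is a free improvement and the omission is not an error

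*Protocol article*

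**What the plan says.** Under General rules of the statistical analyses, all outcomes are analysed uncorrected and also "jointly corrected for risk factors (type and severity of illness, age, BMI and NRS categories". The terms are then defined: "Type of illness will comprise the diagnostic categories, as stratified and grouped per organ system, as well as the presence or absence of a history" (the history meant is cancer). For severity: "As severity of illness score for this correction, APACHE II will be used". BMI and NRS enter as stated categories. The sections on safety, primary efficacy and secondary efficacy endpoints repeat the same list.

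Sepsis appears in two other places. Under Data collected at study entry: "Sepsis upon admission is labeled as such using modified Bone criteria". In the subgroup plan: "a priori subgroup analysis is planned for patients with and without sepsis upon admission". The stated reason is that sepsis worsens the metabolic effects of early PN. The other subgroup factors are BMI and NRS ("A priori defined subgroup analyses will be performed for BMI and NRS subcategories") and "patients admitted to ICU after emergency or elective cardiac surgery as compared with all other patients".

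The 17 strata under Randomization are organ systems or referral disciplines. None is a sepsis or infection category.

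**The concern.** The plan regards sepsis on admission as important enough for a prespecified subgroup analysis and records it for the patients at entry, yet leaves it out of the corrected model. The subgroup models hold only the factor, the intervention and their interaction, without other variables. As planned, therefore, sepsis and the correction set never stand in the same model.

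In Cox and logistic models, leaving out a prognostic baseline variable pulls the estimated treatment effect towards the null even when the arms are balanced. What is at stake is some power in the corrected analyses, chiefly the corrected Cox analysis of time to discharge alive from ICU. The validity of the result is not at stake.

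**Working it through.** **1. The plan's own figure, and whether it depends on the set.** Inputs from Sample size calculation: ICU mortality 20% against 23%, 70% power, two-sided 5%.

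n per arm = [1.960·√(2·0.215·0.785) + 0.524·√(0.20·0.80 + 0.23·0.77)]² / 0.03² = (1.139 + 0.304)² / 0.0009 ≈ 2315, or 4630 in total against 4640 stated.

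For ICU stay (SD 13, difference 1 day, one-tailed): SE = 13·√(2/2320) = 0.382, so power = Φ(1/0.382 − 1.645) = 0.835, consistent with at least 80%.

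Both figures reproduce. Neither takes credit for covariate correction, so the choice of set does not touch them.

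**2. Set and baseline data side by side.**

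| Subgroup factor | In the correction set? |
|---|---|
| BMI | Yes |
| NRS | Yes |
| Cardiac surgery | Through diagnostic category, unless grouping per organ system merges it with other cardiovascular admissions |
| Sepsis on admission | No |

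**3. How the loss arises.** Simulated Cox trials, all inputs on sepsis assumed: N = 4640, true log hazard ratio for treatment 0.085, 85% events, a severity score in the model, sepsis in about 20% and correlated with severity, sepsis hazard ratio for discharge 0.7, 300 replicates.

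| Model | Mean log HR | SE | Mean z |
|---|---|---|---|
| Treatment only | 0.0663 | 0.0319 | 2.080 |
| + severity | 0.0817 | 0.0319 | 2.564 |
| + severity + sepsis | 0.0831 | 0.0319 | 2.608 |

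The SE is unchanged; only the estimate moves. Information ratio = (mean z with / mean z without)². For sepsis this is (2.608/2.564)² = 1.035. For the severity score it is (2.564/2.080)² = 1.52. Most of the gain therefore comes from a variable already planned. Power ≈ Φ(mean z − 1.96) goes from Φ(0.604) = 0.727 to Φ(0.648) = 0.742, about 1.4 points. Counting rejections in the 300 replicates gave 73.0% and 75.7%, but that difference is noisy.

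**4. Range over the unknown inputs.** A check with 1000 replicates per setting: N = 4640, treatment HR 1.10, 80% events, severity in the model (log HR −0.6 per SD), latent sepsis correlated 0.4 with severity. Power is from Φ(mean z − 1.96). The Monte Carlo error of the ratio is 0.002 to 0.009.

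| Prevalence | Sepsis HR | Information ratio | Power without → with |
|---|---|---|---|
| 10% | 0.8 | 1.004 | 82.1 → 82.2% |
| 35% | 0.8 | 1.010 | 81.7 → 82.1% |
| 20% | 0.7 | 1.018 | 81.5 → 82.2% |
| 35% | 0.7 | 1.028 | 81.0 → 82.0% |
| 10% | 0.6 | 1.021 | 81.4 → 82.2% |
| 20% | 0.6 | 1.038 | 80.7 → 82.1% |
| 35% | 0.6 | 1.061 | 79.6 → 81.9% |
| 10% | 0.5 | 1.038 | 80.8 → 82.2% |
| 20% | 0.5 | 1.074 | 79.3 → 82.0% |
| 35% | 0.5 | 1.119 | 77.4 → 81.8% |

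The treatment SE was 0.0329 in every model. Stronger overlap with severity shrinks the gain: at correlation 0.5, separate runs gave 3.1%, 1.3% and 0.4% at HR 0.6, 0.7 and 0.8. For logistic mortality models the gain was only about 1 to 2%.

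**5. In patients.** 3% of 4640 is 139; 8% is 371; 12% is 557.

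**The case against.** The strongest case against is that nothing here is wrong. The plan prespecifies one reasoned set, uses it consistently and reports every outcome uncorrected as well. A factor chosen because the effect may differ across it need not predict outcome beyond APACHE II and diagnosis, and the planned interaction model already covers that modifying role for the primary and safety endpoints. APACHE II and the diagnostic categories plausibly carry part of what sepsis would add.

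All of this stands, and it is why the gain is small. It does not argue against adding the variable: one recorded yes/no term among 4640 patients costs almost nothing. The plan also does not treat APACHE II as sufficient, since it adds age, diagnosis and cancer history beside it. The absence of co-linearity required for the corrected ICU and hospital mortality models would be an obstacle only if sepsis nearly duplicated the other terms, and nothing in the document suggests that.

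A reader might also infer that the recorded comorbidities ("presence of cancer, diabetes mellitus, kidney failure (Chronic Kidney Disease score), liver failure (Child classification), COPD (Gold classification") and heart failure should be added to match each organ-specific outcome. The document does not support that. Cancer history is already in the set, the others overlap with APACHE II and the diagnostic categories, and their separate gain has not been sized for those outcomes. Outcome-specific lists would also replace one common model with many in a plan that tests without multiplicity correction. A single common set is a defensible choice.

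**Conclusion.** The point holds as a low-cost efficiency suggestion. Sepsis on admission is recorded, is a planned subgroup factor and is absent from the correction set. The corrected Cox analysis gives up about 0 to 3% of information (0 to 1 power point) over most of the range of independent sepsis hazard ratios from 0.6 to 0.8. The high corner, 35% prevalence with a hazard ratio of 0.6, reaches about 6% (2 points). About 8 to 12% (3 to 5 points) is reached only at a hazard ratio of 0.5 with prevalence of 20 to 35%. Prevalence, strength and correlation with severity are all assumptions, because the document gives none of them.

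Three stronger readings are tempting and unsupported:
- That the omission biases the comparison or is a mistake. Under randomization it creates no false-positive result, and it contradicts nothing in the plan.
- That precision is lost. The standard error did not change; the loss comes through attenuation alone.
- That sepsis is certainly the only subgroup factor left out. This holds only if grouping per organ system keeps cardiac surgery separate.

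**What to change.** Before unblinding, add sepsis on admission (yes/no, as defined at study entry) to the common correction set in General rules of the statistical analyses, and carry it through to the sections on safety, primary efficacy and secondary efficacy endpoints. Keep one common set for all outcomes. The cost is one sentence, with no new data, no change to the sample size and no change to the uncorrected analyses. The article states that the primary efficacy endpoint was not analysed at the interim, so the change can still be prespecified for that endpoint.

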### Primary efficacy endpoint

The primary efficacy endpoint for this RCT is the time to discharge alive from ICU. As the time of ICU discharge to the regular ward may be affected by the availability of beds on the regular wards, which could induce bias, we a priori decided to analyze "time to discharge from ICU" as "time to ready for discharge from ICU". A patient is considered "ready for discharge" as soon as all clinical conditions for ICU discharge have been fulfilled (no longer in need for vital organ support and receiving at least 2/3 of the caloric requirements as oral feeds) or earlier when the patient is actually sent to a regular ward.

Time to discharge alive from ICU will be reported by Kaplan Meier plots, with ICU non-survivors censored beyond the longest ICU stay of survivors and censoring time of patients still in the ICU at closing of the datafile (90 days after last patient inclusion) over both treatment groups. The impact of "late PN" versus "early PN" will be analyzed, with and without correction for age, BMI & NRS categories and type and severity of illness, by Cox proportional hazard analysis. The distribution of the actual time to discharge from ICU will be reported for ICU-survivors and ICU-non-survivors separately. In view of the time window of the randomized intervention in ICU, also the proportion of patients staying beyond 8 days in ICU will be reported.

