### Sample size calculation

The sample size was calculated in order to detect, with at least 80% power and 95% certainty, an increase or decrease in average duration of ICU stay with one day [from a baseline assumed ICU stay of 8 ± 13 (mean ± SD) days and a median of 4 days assuming log-normal distribution; power calculated using one-tailed Student's t-test using the mean and SD for an increase and a decrease with 1 day and confirmed with two-tailed Student's t-test after log transformation]. To concomitantly detect with at least 70% power and 95% certainty an ICU mortality increase or decrease of 3% (assuming a baseline mortality of 20% anticipating a Medical-ICU/Surgical-ICU patients fraction of 25/75%; power calculated with two-tailed chi-square testing), a sample of 4640 (patients 2320 per arm) was considered necessary. We plan to calculate the true power of the study for detection of any eventual smaller difference in these outcomes.

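### The a priori subgroup and interaction analyses are limited to uncorrected models, although the same endpoints are analysed overall both with and without covariate correction

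*Protocol article*

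**What the plan says.** All points below come from the statistical analysis plan in the protocol article.

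- **Overall rule** (General rules of the statistical analyses): "All outcomes will be analyzed in an uncorrected manner as well as jointly corrected for risk factors". The factors are diagnostic category grouped by organ system, history of cancer, APACHE II, age, BMI category and NRS category.
- **Primary endpoint** (Primary efficacy endpoint): the treatment effect on time to live ICU discharge is estimated "with and without correction for age, BMI & NRS categories and type and severity of illness, by Cox proportional hazard analysis". The Safety endpoints section likewise plans mortality analyses with and without correction. Neither version is named as the main one.
- **Subgroups** (General rules): "These a priori defined subgroup analyses will be performed for the primary and safety endpoints without correction for other variables". Each interaction is tested by "logistic regression or proportional hazard analysis as appropriate", "for each subgroup variable separately and with the subgroup variable, the intervention and their interaction in the model". The level is fixed too: "The interaction will be tested at a significance level of 0.1".

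Each interaction model therefore has three terms: subgroup, treatment and their product. The subgroup's own main effect is the only prognostic information in it.

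**The concern.** The exclusion is an explicit choice, not a detail left to a fuller document, and it departs from the plan's own two-version rule without explanation. It falls on tests that the plan itself treats as short of power, since it relaxes their level to 0.1 and dichotomises BMI to gain power. Diagnosis, the stratification factor within site, drops out of these models except where cardiac surgery is itself the subgroup.

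Logistic and Cox models are non-collapsible. Leaving out a strong prognostic factor changes the treatment log-ratio being estimated, even under perfect randomisation, and usually lowers power. At stake is how an interaction result is read. A conditional difference in response may be missed, or one may be signalled that is absent on the conditional scale. With no corrected interaction model planned, a reader cannot tell these apart. The corrected overall result also has no subgroup counterpart.

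**Working it through.** **1. The plan's own figure.** The Sample size calculation section states that "a sample of 4640 (patients 2320 per arm) was considered necessary". For ICU mortality of 20% versus 23%, two-sided 5% and 70% power:

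n per arm = [1.960·√(2·0.215·0.785) + 0.524·√(0.20·0.80 + 0.23·0.77)]² / 0.03² ≈ 2315, or 4630 in total.

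This reproduces 4640. The article gives no power for any interaction, so there is no stated figure to contradict.

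**2. Closed-form guide on log stay.** The plan's mean of 8 and SD of 13 days give a log-normal SD of √ln(1 + (13/8)²) = 1.137. Assumptions: a 50% subgroup (1160 per cell), an interaction of 0.15 on log stay, and a two-sided 0.10 test (the plan does not state sidedness). With R² the share of variance explained by the covariates:

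SE = 1.137·√(4/1160)·√(1 − R²); power = Φ(0.15/SE − 1.645).

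| R² | 0.15/SE | Power |
|---|---|---|
| 0 | 2.25 | 73% |
| 0.10 | 2.37 | 77% |
| 0.20 | 2.51 | 81% |
| 0.30 | 2.69 | 85% |

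This is normal theory, not Cox, so it shows direction and order of size only.

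**3. Simulation in the planned model types, equal prognostic spread.** N = 4640, 40% subgroup, interaction tested at 0.10. One prognostic score is either left out or included.

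| Model | Score SD | True interaction | Estimate without / with score | Power without / with score |
|---|---|---|---|---|
| Logistic, 300 runs | 0.5 | 0.40 | 0.389 / 0.407 | 86% / 89% |
| Logistic, 300 runs | 1.0 | 0.40 | 0.344 / 0.400 | 73% / 83% |
| Cox, 120 runs | 0.8 | 0.15 | 0.118 / 0.155 | 58% / 78% |

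Relative to the fit with the score, the uncorrected estimate is smaller by 1 − 0.389/0.407 = 4%, 1 − 0.344/0.400 = 14%, and 1 − 0.118/0.155 = 24%. The power loss is about 3, 10 and 20 points. In the Cox runs about 16% of patients were never discharged and were censored beyond the longest stay, as the plan prescribes for non-survivors.

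**4. Simulation with unequal prognostic spread.**

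| Model | Score SD in the two groups | Treatment effect in reference group | True interaction | Estimate without / with score | Rejection without / with score |
|---|---|---|---|---|---|
| Logistic | 0.5 and 1.5 | 0.5 | 0 | −0.11 / 0.00 | 15% / 10% |
| Logistic | 0.5 and 1.5 | 0.5 | −0.20 | −0.25 / −0.19 | 59% / 36% |
| Cox | 0.4 and 1.2 | 0.2 | 0 | −0.03 / 0.00 | 16% / 7% |

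Here the uncorrected interaction moves away from zero, even when the conditional interaction is nil.

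**5. Precision and limits.** Monte Carlo error on power is about √(0.8·0.2/300) = 2 points for the logistic runs and √(0.5·0.5/120) = 5 points for the Cox runs. A smaller Cox exercise (60 runs, error about 5 points) let the risk of death depend on the score. With equal spread, power was 23% without and 37% with the score. With unequal spread and no interaction, rejection was 18% without and 20% with it. Correction therefore does not guarantee the nominal level when the score also drives death.

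**The case against.** The strongest defence is that a simple, prespecified, uncorrected interaction test is transparent and valid. Randomisation protects the within-subgroup marginal comparisons, and a specific exception to a general rule is not a contradiction. All of that stands.

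A reader might go further than the article allows in three ways.

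- **That the main analysis is the corrected one, so subgroup and overall hazard ratios are on different scales.** The plan produces both overall versions and ranks neither. The uncorrected subgroup estimates can be set beside the uncorrected overall estimate. The mismatch exists only against the corrected result.
- **That omitting covariates always pulls the interaction toward zero.** Each subgroup's own treatment effect is attenuated, but the difference between two attenuated effects need not be. Step 4 shows it growing and appearing from nothing. Unequal spread is plausible for cardiac surgery versus all others, a subgroup whose shorter ICU stay the plan itself notes.
- **That a definite minimum gain in power is assured.** The article gives no prognostic strength, subgroup prevalence or interaction size. One logistic scenario gained only 3 points, which is close to simulation error.

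It is also fair to object that correction needs more than deleting a clause. Cardiac surgery is itself a diagnostic category. The plan's rule for underrepresented categories moves patients to the next in rank, which has no meaning for unordered diagnoses. The Safety endpoints section makes corrected logistic models conditional on absence of co-linearity. These points stand and shape the fix.

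**Conclusion.** The point holds as a weakness of efficiency and consistency in a declared choice. The plan defines a corrected analysis for the primary and mortality endpoints and then withholds it, without a reason, from the interaction tests.

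The likely cost is roughly 3 to 20 points of interaction power when prognostic strength is similar across subgroups. Where it differs, the uncorrected interaction may be smaller or larger than the conditional one, or present where that is nil. These sizes rest on assumed score strengths (SD 0.5 to 1.0 with equal spread), an assumed 40% subgroup and assumed interactions of 0.40 (log odds ratio) and 0.15 (log hazard ratio). The article neither supports nor excludes them.

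Nothing here makes the uncorrected subgroup results invalid for marginal effects, and the direction of any distortion in this trial cannot be stated in advance.

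**What to change.** In the subgroup paragraph of the General rules, replace the clause excluding correction with a rule along these lines:

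- Each interaction model is fitted uncorrected and also corrected for the covariates already listed in that section. Both are reported, and the corrected interaction test is prespecified as the one to interpret.
- In the BMI and NRS models, the dichotomised subgroup variable replaces its own categorical covariate.
- In the cardiac surgery model, the remaining diagnostic categories stay as covariates within the non-cardiac group.
- In the sepsis model, the full covariate set is used, since sepsis is not among the listed factors.
- Sparse diagnostic categories are merged by organ system. The next-in-rank rule is kept for BMI and NRS only.
- The co-linearity condition in the Safety endpoints section applies to these models as well.

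The cost is wording and a few extra model fits, with no new data. The downside is some loss of diagnostic detail where categories are merged. The change should be made before the data file is finalised, so that it remains prespecified.
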